**Study Population:**

Adult patients (aged ≥18 years) within 100 days after allogeneic HSCT, without active SARS-CoV-2 infection at enrollment.

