**Ⅳ. Study Design and Methodology**

4.1 Study Design

This is a prospective, single-center, open-label, randomized controlled trial evaluating the prophylactic efficacy and safety of COVID-19 convalescent plasma (CCP) in adult patients early after allogeneic hematopoietic stem-cell transplantation (HSCT).

Eligible participants are randomized in a 1:1 ratio to receive either:

Experimental group (CCP group): Standard supportive care plus four planned CCP infusions.

Control group: Standard supportive care without CCP.

The total study duration for each participant is 12 months after transplantation. Participants will be followed for clinical outcomes, infection status, and safety events throughout the observation period.

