4.2 Randomization and Allocation Concealment

Randomization is performed using a computer-generated sequence prepared by an independent statistician who is not involved in patient care.

Allocation follows a simple randomization design with a 1:1 ratio between the CCP group and the control group. The randomization sequence is stored securely by the data manager and concealed until the time of patient enrollment.

Upon confirmation of eligibility and signed informed consent, the investigator obtains the next available randomization code from the sealed allocation list. This process ensures that treatment assignment remains concealed until enrollment is finalized.

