4.4 Intervention

4.4.1 Experimental Group (CCP Group)

Participants receive standard supportive care plus four infusions of high-titer COVID-19 convalescent plasma (CCP).

Dosage: 200 mL per infusion.

Infusion schedule:

1. Day +14 ± 2 days
2. Day +28 ± 2 days
3. ~2 months (±7 days)
4. ~3 months (±7 days)

Each CCP unit must meet the following criteria:

Collected from donors who have fully recovered from COVID-19 and are at least 14 days symptom-free.

Confirmed SARS-CoV-2 PCR negative at the time of donation.

Tested positive for anti–SARS-CoV-2 IgG with high antibody titer (S/CO ≥ 12) according to ELISA testing standards.

ABO compatible with the recipient.

Infusions are administered intravenously at a rate not exceeding 2 mL/kg/hour, with continuous monitoring for transfusion reactions.

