4.6 Safety Monitoring

All adverse events (AEs) and serious adverse events (SAEs) occurring during or after CCP infusion will be recorded.

Events are graded according to Common Terminology Criteria for Adverse Events (CTCAE) version 5.0, categorized by severity (Grade 1–5) and relationship to the study intervention (definite, probable, possible, unrelated).

All SAEs are reported within 24 hours to the principal investigator and reviewed by the institutional ethics committee.

An independent Data and Safety Monitoring Board (DSMB) oversees trial conduct and safety data.

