4.7 Follow-Up and Assessments

| **Time Point** | **Clinical Assessments** | **Laboratory Assessments** |
| --- | --- | --- |
| Baseline (pre-transplant) | Demographics, medical history, HSCT details, donor type | SARS-CoV-2 antibody titer, PCR test |
| Day +14 | Vital signs, infusion tolerance | Antibody titer, CBC, liver/renal function |
| Day +28 | AE assessment, infection monitoring | Antibody titer, PCR test |
| 2 months | Clinical evaluation, GVHD status | Antibody titer, PCR test |
| 3 months | Clinical evaluation | Antibody titer, PCR test |
| 6 months | Infection and survival status | Antibody titer |
| 12 months | Final follow-up | Antibody titer, survival status |

COVID-19 infection is defined as PCR-confirmed SARS-CoV-2 positivity by nasopharyngeal swab or other approved method.

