5.2 Analysis Populations

Three analysis populations will be defined:

1. Intention-to-Treat (ITT) population:

Includes all randomized participants, analyzed according to the group to which they were originally assigned, regardless of treatment received.

2. Per-Protocol (PP) population:

Includes participants who complete all planned study procedures and at least four CCP infusions (for the CCP arm) without major protocol violations.

3. Safety population:

Includes all participants who receive at least one CCP infusion (in the experimental group) or standard care (in the control group), used for safety analyses.

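### The safety population has unequal entry rules for the two arms and no common start of observation, so between-arm safety comparisons made in it can be biased

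*Protocol*

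**What the plan says.** Section 5.2 of the protocol sets different conditions for entering the safety population in each arm: "Includes all participants who receive at least one CCP infusion (in the experimental group) or standard care (in the control group), used for safety analyses". The ITT definition in the same section is symmetric: "Includes all randomized participants, analyzed according to the group to which they were originally assigned, regardless of treatment received".

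Section 4.1 gives standard care to the plasma arm as well: "Experimental group (CCP group): Standard supportive care plus four planned CCP infusions". Section 4.4.1 places the first infusion at day +14, with a window of 2 days either side.

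The day of randomisation is not fixed:
- Section 4.2: "Upon confirmation of eligibility and signed informed consent, the investigator obtains the next available randomization code from the sealed allocation list". No transplant day is named.
- Section 4.7 puts the baseline visit, with its study PCR and antibody tests, before transplant.
- The Study Summary describes the population as "Adult patients (aged ≥18 years) within 100 days after allogeneic HSCT, without active SARS-CoV-2 infection at enrollment".

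The start of safety recording is not fixed either. Section 4.1 says that participants, without distinction of arm, are followed for safety events over the whole observation period. Section 4.6 ties recording to plasma: "All adverse events (AEs) and serious adverse events (SAEs) occurring during or after CCP infusion will be recorded". The first adverse event assessment listed in Section 4.7 is at day +28.

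**The concern.** Standard care goes to both arms, so the control condition excludes practically nobody, while the CCP condition excludes everyone who dies, becomes unfit or leaves before the first infusion. Any time between randomisation and first infusion is then free of excluding events by construction in the CCP safety set, but not in the control set.

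This matters wherever the set is used to compare arms on events of any cause. The listed safety endpoint (Section 3.4) concerns plasma-related events, but Section 3.2 also covers systemic adverse events, and Section 4.6 grades events 1 to 5. Controls are in the safety set, and their presence serves little purpose unless the arms are to be compared. With 36 patients per arm, one or two patients visibly move a percentage.

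**Working it through.** The plan states no figure on this point, so there is none to reproduce. The check has two parts.

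**1. Is there a gap between randomisation and first infusion?**
- For a gap: the baseline tests are pre-transplant (4.7); consent must precede any study procedure (6.2); the code is drawn once eligibility and consent are in place (4.2). A patient randomised after day 14 + 2 = +16 could not receive the first infusion within its window (4.4.1).
- Against a gap: the Study Summary allows enrolment up to day 100 after transplant.
- Result: a gap is likely but not certain. If everyone were randomised at the day +14 visit, it would be close to zero.

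**2. How large could the distortion be?**

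Inputs: 36 per arm (Section 5.1). Assumed, because the documents give no rates:
- q = share of each arm that has an event between randomisation and day +14 and would not reach a first infusion;
- r = later event rate among the rest, equal in both arms.

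*Case A: early control events are recorded (Section 4.1 governs).*
- Control rate = q + (1 − q)r
- CCP rate in the safety set = r
- Spurious gap = q(1 − r)

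| q | CCP patients dropped (36q) | Control, r = 10% | CCP | Gap, r = 10% | Gap, r = 20% |
|---|---|---|---|---|---|
| 2% | 0.7 | 11.8% | 10% | 1.8 points | 1.6 points |
| 5% | 1.8 | 14.5% | 10% | 4.5 points | 4.0 points |
| 10% | 3.6 | 19.0% | 10% | 9.0 points | 8.0 points |

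In whole patients, with 2 early and 4 later deaths assumed in each arm: CCP 4/(36 − 2) = 4/34 = 11.8%; control (2 + 4)/36 = 16.7%. The apparent difference is 4.9 points with identical true mortality.

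*Case B: early control events are not recorded (Section 4.6 governs), and the affected controls have no later event.*
- Control rate = (1 − q)r; CCP rate = r; gap = −qr
- At r = 10% and q = 2%, 5%, 10%: −0.2, −0.5, −1.0 points

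The sign reverses, because those controls stay in the denominator without contributing events. The same formula holds for patients who withdraw early without an event.

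**Check of the remedy, with the same counts and all events recorded:** all randomised, 6/36 against 6/36; day +14 landmark in both arms, 4/34 against 4/34. The gap is zero either way.

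**The case against.** The strongest counter-arguments are these.

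- *Early deaths are not lost to the trial.* Overall survival is a separate secondary endpoint, and the ITT analysis keeps early CCP-arm deaths. This stands. The distortion is confined to tables built on the safety population, where Grade 5 counts could then disagree with the survival analysis.
- *The listed safety endpoint is plasma-related events.* Uninfused patients cannot have them, so an infused-only denominator is right for that endpoint. This also stands, and it limits the point to all-cause comparisons.
- *Randomisation may coincide with the first infusion.* This is possible, but no section says so, and the pre-transplant baseline points the other way.
- *Early control toxicity may never be recorded.* Section 4.6 permits that reading, and Case B shows that the direction then reverses. The set still has no common start of observation.

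A reader might infer that early deaths and toxicity count against controls only, and that the plan therefore makes plasma look safer than it is. The documents do not support that: it needs randomisation before day +14 and full recording of control events, and neither is fixed. A reader might also infer a rule that safety events are sorted by assigned arm, so that a control given plasma would have a reaction counted as a control event. The group labels in parentheses only imply such sorting, and Section 4.4.2 provides for no plasma in controls.

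**Conclusion.** The concern holds in limited form. Section 5.2 fixes unequal entry rules for the safety population, and the protocol gives no common start of observation for the two arms. If patients are randomised before day +14, a between-arm comparison of all-cause AEs, SAEs or Grade 5 events in this set is biased.

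If early control events are recorded, the bias favours plasma by 1.8 to 9.0 points for early-event shares of 2% to 10% and a later rate of 10%. If they are not, the control rate is understated, by 0.2 to 1.0 points under the same shares. All these rates are assumptions. If everyone is randomised at the first infusion visit, the bias is near zero. Overall survival by ITT and plasma-related event rates are untouched.

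**What to change.** In Section 5.2, base between-arm safety comparisons on one of two sets:

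1. all randomised participants, by assigned arm, with events counted from randomisation; or
2. participants of both arms who are alive and on study at a common day +14 landmark, still by assigned arm, with earlier events listed by assigned arm.

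The second option works only if everyone is randomised by the landmark. In neither option should patients be regrouped by plasma actually received: that would move CCP-assigned patients too ill for infusion into the comparator and create a new bias.

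Keep the at-least-one-infusion set for infusion-reaction and plasma-related event rates only. Reconcile the Study Population statement with Sections 4.1, 4.2, 4.6 and 4.7, so that the document says when randomisation takes place and when adverse event recording starts in each arm.

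The cost is a wording change, one extra listing, and slight dilution from the few CCP-assigned patients never infused. No new data are needed if control safety events are followed as Section 4.1 says; if Section 4.6 has been applied literally, recording of control events has to be added.

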5.3 Statistical Methods

1. Descriptive Statistics:

Continuous variables will be summarized as mean ± standard deviation (SD) or median (interquartile range, IQR) as appropriate.

Categorical variables will be summarized as counts and percentages.

2. Group Comparisons:

Continuous variables: Student’st-test (normally distributed) or Mann–WhitneyU test (non-normally distributed).

Categorical variables: Chi-square (χ²) or Fisher’s exact test.

Time-to-event data (e.g., infection-free survival): Kaplan–Meier analysis and log-rank test.

3. Multivariate Analysis:

Cox proportional-hazards regression will be used to identify independent factors associated with infection risk or survival.

Variables withP < 0.10 in univariate analysis will be included in the multivariate model.

4. Confidence Intervals:

Two-sided P values < 0.05 will be considered statistically significant.

For all main comparisons, 95% confidence intervals (CIs) will be reported alongside P values.

5. Correction for Multiple Comparisons:

When multiple secondary endpoints are analyzed,P values will be adjusted using the Benjamini–Hochberg false discovery rate (FDR) method to control for type I error.

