**Secondary Endpoints:**

1. Incidence and severity of COVID-19 (mild/moderate/severe).
2. Overall survival (OS) at one year.
3. Time to first SARS-CoV-2 infection.
4. Incidence of adverse events related to plasma infusion.
5. SARS-CoV-2 antibody titers and their kinetics over time.

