**Statistical Analysis:**

Both intention-to-treat (ITT) and per-protocol (PP) analyses will be performed. Kaplan–Meier survival curves will be generated, and group comparisons will use the log-rank test. Continuous variables will be compared using the t-test or Mann–Whitney U test; categorical variables using χ² or Fisher’s exact test.

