3.2 Secondary Objectives

1. To assess the severity and clinical course of COVID-19 infection (mild, moderate, severe, or critical) in CCP versus control groups.

2. To evaluate overall survival (OS) at one year post-transplant.

3. To determine the time to first SARS-CoV-2 infection after transplantation.

4. To assess the kinetics and durability of anti–SARS-CoV-2 antibody levels following CCP infusion.

5. To evaluate the safety and tolerability of CCP administration by recording infusion-related and systemic adverse events.

6. To explore correlations between antibody titers and clinical outcomes.

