3.4 Secondary Endpoints

1. COVID-19 severity grading according to WHO Clinical Progression Scale (scores 1–10).

2. Overall survival rate at 12 months post-transplant.

3. Time to first COVID-19 diagnosis (days from transplantation to first positive test).

4. Quantitative or semiquantitative SARS-CoV-2 antibody titers measured at predefined intervals (baseline, pre-infusion, and 14, 28, 60, 90, 180, and 365 days post-transplant).

5. Number and proportion of adverse events (AEs) and serious adverse events (SAEs) related to plasma infusion, graded according to CTCAE v5.0.

6. Association between CCP antibody titer and risk reduction for COVID-19 infection or severe disease.

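### The only test stated for continuous data compares the arms one visit at a time, which fits poorly with a secondary objective on antibody kinetics and durability

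*Protocol*

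**What the plan says.** **What is to be learned.** Protocol section 3.2, objective 4, is "To assess the kinetics and durability of anti–SARS-CoV-2 antibody levels following CCP infusion". The Study Summary lists as a secondary endpoint "SARS-CoV-2 antibody titers and their kinetics over time". Under section 3.4, titres are "measured at predefined intervals (baseline, pre-infusion, and 14, 28, 60, 90, 180, and 365 days post-transplant". The section 4.7 table has a pre-transplant baseline row with "SARS-CoV-2 antibody titer, PCR test", and a titre at each of the six later visits (days 14 and 28; months 2, 3, 6 and 12). The Figure 1 caption adds weekly antibody testing to day +120.

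**How it is to be analysed.** Section 5.3, item 2, gives the rule for comparing groups: "Continuous variables: Student’st-test (normally distributed) or Mann–WhitneyU test (non-normally distributed". The Study Summary repeats it: "Continuous variables will be compared using the t-test or Mann–Whitney U test". For description, section 5.3 has "Continuous variables will be summarized as mean ± standard deviation (SD) or median (interquartile range, IQR) as appropriate". The one regression model serves other outcomes: "Cox proportional-hazards regression will be used to identify independent factors associated with infection risk or survival". Item 5 of section 5.3 applies Benjamini–Hochberg when several secondary endpoints are analysed and does not mention repeated visits within one endpoint.

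The protocol defines no per-patient summary of titre (slope, area under the curve, change from baseline) and no adjustment for the baseline titre.

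**The concern.** Kinetics and durability describe how titre changes within a patient over time. A two-sample test describes how two groups differ at one time. Applied to titre, the stated rule yields six arm contrasts and no rate of decline. It also does not address the part of the objective that lies within the CCP arm, namely how titre behaves after infusion.

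This matters because section 2.3 bases the repeat infusions on waning antibody (IgG half-life of about 21 days) and on maintaining protection through the early post-transplant phase. The titre time course is the trial's direct check of that reasoning. The stated rule leaves it to descriptive summaries and sets aside the baseline measurement already collected.

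**Working it through.** The protocol states no figure that depends on this point, so there is none to reproduce. The figures below show the size of the issue. The within-patient correlation ρ of log titre is not in the document; values of 0.3, 0.5 and 0.7 are assumed.

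**1. Number of visits.** Section 3.4 names days 14, 28, 60, 90, 180 and 365, which is six. The pre-infusion samples are not counted as a further visit: infusions fall on about days 14, 28, 60 and 90, and controls have none.

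**2. Precision given up by not using baseline.** The variance of a baseline-adjusted arm difference, relative to the unadjusted one at the same visit, is 1 − ρ², so the reduction is ρ².

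| Assumed ρ | Variance ratio 1 − ρ² | Reduction | Interval narrower by 1 − √(1 − ρ²) |
| --- | --- | --- | --- |
| 0.3 | 0.91 | 9% | 5% |
| 0.5 | 0.75 | 25% | 13% |
| 0.7 | 0.51 | 49% | 29% |

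Here ρ is the correlation between the pre-transplant titre and the titre at the visit. Sections 2.2 and 2.3 describe minimal endogenous antibody production early after transplant, and one arm receives high-titre plasma. The true value may therefore be low, and the gain small.

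**3. Validity of the tests.** Simulation with 36 per arm, six visits, equal correlation between visits, no arm difference and 20,000 runs. A t-test at one visit rejected in 4.8–5.1% of runs, and a t-test on one mean per patient also in 4.8–5.1%. Both hold their level.

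**4. Six tests without correction.** In the same simulation, at least one of six visits gave P<0.05 in 24.2% (ρ = 0.3), 20.9% (ρ = 0.5) and 16.4% (ρ = 0.7) of runs. Independence would give 1 − 0.95⁶ = 26.5%. These figures assume no difference at any visit, which is unlikely while transfused antibody persists. With the protocol's half-life of about 21 days and a last infusion near day 90, the fraction remaining at day 180 is 2^(−90/21) ≈ 5%, and at day 365 it is 2^(−275/21) ≈ 0.01%. A null is therefore plausible mainly at the last two visits, where the chance is at most about 1 − 0.95² ≈ 10%.

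**5. Effect on the false discovery rate procedure.** Section 3.4 lists six secondary endpoints. For illustration, give each of the other five one P value. If titre contributes one P value, the family has 6 members; if it contributes six, the family has 11. Suppose the titre P values are all very small, as the design would lead one to expect. The smallest non-titre P value is then judged against 2/6 × 0.05 = 0.017 in the first case and 7/11 × 0.05 = 0.032 in the second. The unstated choice changes the hurdle for other endpoints, including survival.

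**6. Infection during follow-up.** Section 5.1 assumes that 80% of controls and 50% of CCP patients are infected within a year: 0.80 × 36 ≈ 29 and 0.50 × 36 = 18. If infection raises titre, arm contrasts at late visits mix transfused antibody with response to infection, and more so in controls.

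**The case against.** The strongest objection is that section 5.3 is a generic rule that never mentions titre, and that a longitudinal model for a secondary immunology endpoint is ordinary SAP content. That is fair as far as it goes: the absence of a model from the protocol is not the point. What remains is that the protocol states its rule twice, with no exception for titre and no deferral to another document. A SAP with a better analysis would have to depart from it.

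A reader might infer three stronger things that the document does not support.

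- *That the stated tests are invalid for titre, or that the objective cannot be addressed at all.* A two-sample test at one visit is valid under randomisation with or without baseline. The same tests would be valid on a per-patient change, slope or area under the curve. Per-visit means or medians can also describe a time course. The protocol simply defines no such summary and gives no estimate of decline.
- *That repeated titres will be pooled as if independent, or that two visits in the same patients will be compared as if they were separate groups.* Pooling six visits would raise the type I error to about 22–36% in the simulation above. The protocol proposes neither analysis, so these errors cannot be charged to it.
- *That a mixed model would cure the loss of patients by death.* It would not, because titre after death is undefined.

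It is also fair to say that section 3.4 allows semiquantitative titres and section 3.5 mentions binding absorbance values. A rank-based test may suit such data better than a log-normal model.

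**Conclusion.** The stated rule does not match the objective. It gives valid but separate arm comparisons at six visits, leaves the baseline titre unused, estimates no decline, and does not settle how many titre P values enter the secondary-endpoint correction.

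The size is moderate and depends on assumptions. The variance forgone per visit is 9–49% for correlations of 0.3 to 0.7, and could be negligible below that. The 16–24% chance of a stray significant visit applies only if the arms differ at no visit and no correction is made across visits.

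The primary endpoint, the sample size and the safety analysis are unaffected. The change should be made because it is cheap, but the trial does not fail without it.

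**What to change.** Exempt antibody titre from the t-test/Mann–Whitney rule in section 5.3 and in the Study Summary, and state in its place:

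- One repeated-measures model of log titre over the scheduled visits, with arm, visit, arm-by-visit and baseline log titre as fixed effects and a within-patient covariance structure. Report geometric mean ratios by visit with 95% confidence intervals.
- One overall test from that model as the single titre P value entering the Benjamini–Hochberg correction.
- Decline in the CCP arm after the last infusion, with a 95% confidence interval, estimated from samples taken before first SARS-CoV-2 infection.
- Late-visit results described as applying to patients alive and sampled.
- A rank-based or ordinal analysis as a sensitivity check if the assay is semiquantitative or has a ceiling.

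The cost is a few sentences and some analysis time. No extra samples or patients are needed, and R is already named in section 5.6. There are two downsides. The model makes a distributional assumption, which can be checked on residuals. Restricting the decline estimate to pre-infection samples also thins the late data: at the planning rate, about 18 of 36 CCP patients would still be uninfected at one year, before deaths and withdrawals.

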**Ⅲ. Study Objectives and Endpoints**

3.1 Primary Objective

To evaluate whether prophylactic infusion of high-titer COVID-19 convalescent plasma (CCP) reduces the incidence of laboratory-confirmed SARS-CoV-2 infection within one year after allogeneic hematopoietic stem-cell transplantation (HSCT), compared with standard supportive care alone.

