3.3 Primary Endpoint

Incidence of laboratory-confirmed SARS-CoV-2 infection within 12 months after HSCT.

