5.4 Missing Data

No imputation will be performed for missing primary endpoint data.

Participants who withdraw before infection assessment will be censored at the date of last follow-up.

Sensitivity analyses will compare results between complete-case and ITT datasets to ensure robustness.

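### Section 5.3 names only Kaplan–Meier and log-rank, with infection-free survival as the example, while the endpoints count infection alone and no rule covers death without infection

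*Protocol*

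**What the plan says.** The primary endpoint in Protocol section 3.3 is "Incidence of laboratory-confirmed SARS-CoV-2 infection within 12 months after HSCT". Section 4.7 fixes the event: "COVID-19 infection is defined as PCR-confirmed SARS-CoV-2 positivity by nasopharyngeal swab or other approved method". Time to first infection, a secondary endpoint in section 3.4, runs from transplantation to the first positive test. Death enters neither definition. It has its own secondary endpoint, "Overall survival rate at 12 months post-transplant".

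For analysis, section 5.3 lists methods by type of data. The entry that concerns us is "Time-to-event data (e.g., infection-free survival): Kaplan–Meier analysis and log-rank test". The study summary says the same in general terms: "Kaplan–Meier survival curves will be generated, and group comparisons will use the log-rank test". Section 5.1 sizes the trial with a log-rank test on infection rates of 80% and 50%.

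The only censoring rule is in section 5.4: "Participants who withdraw before infection assessment will be censored at the date of last follow-up". It concerns withdrawal. No section says whether a participant who dies uninfected is censored, counted as an event, or treated as having had a competing event.

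**The concern.** The protocol expects deaths. Sections 2.1 and 2.2 describe recipients as at high risk of dying, and one-year survival is an endpoint. A participant who dies uninfected can no longer become infected, so the status of that death has to be fixed before a time-to-infection curve means anything.

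The endpoint sections and section 5.3 point in different directions. Infection-free survival, in its usual sense, counts death as a failure, and it appears in no endpoint list. Time to first infection does not count death. An analyst following section 5.3 could take either route:

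- **Deaths censored.** One minus Kaplan–Meier estimates the infection risk that would apply if nobody died uninfected. That exceeds the proportion actually infected within the year, which is what section 3.3 asks for.
- **Deaths as events.** The quantity is a composite that the protocol does not define and did not use for its sample size. Deaths that plasma does not affect pull the hazard ratio toward 1.

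The trial is open-label (section 4.3), so the choice should not be left until outcomes by arm are known.

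**Working it through.** **Inputs from the protocol.** One-year infection rates 80% (control) and 50% (plasma); two-sided α = 0.05; power 80%; log-rank test; 72 participants, 36 per arm (all section 5.1).

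**Assumptions.** Constant hazards. The protocol gives no rate of death without infection, so q, the one-year risk of such death in the absence of infection, is set at 10%, 20% and 30%, equal in both arms. The 80% and 50% are taken as one minus Kaplan–Meier values. No dropout.

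**The plan's own figure.** Infection hazards are λ = −ln(0.2) = 1.609 and −ln(0.5) = 0.693, so HR = 0.693/1.609 = 0.431. Schoenfeld events needed: 4(1.960 + 0.842)²/(ln 0.431)² = 44.2, rounded up to 45. With mean event probability 0.65, this is 69–70 participants. At 72, expected events are 72 × 0.65 = 46.8, and power is Φ(½√46.8 × |ln 0.431| − 1.960) = 82.2%. So 72 is close to the Schoenfeld figure before any attrition, and 82% is the baseline below. (Whether 72 also covers the stated 10% attrition is a separate matter.)

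**Reading A: deaths censored.** With μ = −ln(1 − q), the actual cumulative incidence of infection is CIF = λ/(λ + μ) × [1 − exp(−(λ + μ))].

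For q = 20%, μ = 0.223:
- control: 1.609/1.833 × 0.840 = 73.8%
- plasma: 0.693/0.916 × 0.600 = 45.4%

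| q | 1 − KM, control / plasma | CIF, control / plasma | Excess (points) | Infections in 72 | Power |
|---|---|---|---|---|---|
| 0% | 80 / 50 | 80 / 50 | 0 / 0 | 46.8 | 82.2% |
| 10% | 80 / 50 | 77.0 / 47.7 | 3.0 / 2.3 | 44.9 | 80.6% |
| 20% | 80 / 50 | 73.8 / 45.4 | 6.2 / 4.6 | 42.9 | 78.8% |
| 30% | 80 / 50 | 70.4 / 42.9 | 9.6 / 7.1 | 40.8 | 76.7% |

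The difference between arms moves less than the levels do: 30 points becomes 29.3, 28.4 and 27.5. The cause-specific HR stays at 0.431; power slips only because there are fewer infections.

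**Reading B: deaths counted as events.** The composite risk is 1 − exp(−(λ + μ)), and HR = (0.693 + μ)/(1.609 + μ). Events are 36 × the sum of the two risks.

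For q = 20%: HR = 0.916/1.833 = 0.50; events = 36 × (0.84 + 0.60) = 51.8; power = Φ(½√51.8 × |ln 0.50| − 1.960) = 70.4%.

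| q | Composite risk, control / plasma | HR | Events in 72 | Power |
|---|---|---|---|---|
| 0% | 80% / 50% | 0.43 | 46.8 | 82.2% |
| 10% | 82% / 55% | 0.47 | 49.3 | 76.5% |
| 20% | 84% / 60% | 0.50 | 51.8 | 70.4% |
| 30% | 86% / 65% | 0.53 | 54.4 | 63.8% |

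There are more events than in reading A but less power, because the added events do not separate the arms.

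**The case against.** The strongest reply is that section 5.3 is a generic list of methods. Infection-free survival is introduced there only as an example, is not assigned to the primary analysis, and may be a loose label for time to first infection. The same list offers counts, percentages and chi-square or Fisher tests, which suit a one-year incidence. If the headline figure is a crude proportion, the Kaplan–Meier excess does not arise in it. The coding of deaths may also be settled in an analysis plan that is not shown. All of this stands, and it rules out saying that the primary result will be biased. It does not remove the mismatch: the example is the only one given, it is not a listed endpoint, and section 5.1 attaches the log-rank test to the comparison on which the trial was sized.

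Three stronger readings are tempting and are not supported:

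- **That the protocol censors deaths.** Section 5.4 speaks of participants who withdraw, not of those who die.
- **That the planned test is invalid.** With deaths censored, the log-rank test is a valid comparison of cause-specific infection hazards. The problem under that reading lies in the incidence estimate.
- **That a mortality difference would pass unnoticed.** Overall survival is a secondary endpoint, and the safety board reviews infection and survival data (section 5.5). What would be missing is the split between deaths without infection and deaths after it.

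The magnitudes also depend on taking 80% and 50% as Kaplan–Meier values. Section 5.1 calls them only infection rates; if they are observed proportions, the Kaplan–Meier figures would lie above them.

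**Conclusion.** The point holds as a mismatch between sections 3.3 and 3.4 and section 5.3, together with a missing rule for death without infection. The consequence is conditional on which reading is applied, and the protocol does not settle that.

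Over an assumed 10% to 30% risk of death without infection, censoring deaths raises the Kaplan–Meier incidence by about 2 to 10 points, with little effect on power. Counting deaths as events does more: it replaces the endpoint with an undefined composite and costs roughly 6 to 18 points of power from a baseline of 82%. These sizes rest on constant hazards, equal mortality in both arms and full follow-up of 72 participants. The direction of the incidence excess needs only that some participants die uninfected while still under risk of infection. The change is worth making but is not a fatal flaw.

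**What to change.** 1. In section 5.3, state that one-year infection incidence is estimated by the cumulative incidence function (Aalen–Johansen), with death without infection as a competing event, and give it by arm with 95% confidence intervals.
2. Keep the planned log-rank test, described as a cause-specific comparison of infection with deaths censored. Say the same in section 5.4, next to the rule for withdrawals.
3. Report the cumulative incidence of death without infection by arm beside the infection result.
4. Either delete infection-free survival from section 5.3 or add it to section 3.4 as a separately defined secondary composite.

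The cost is analysis wording. Section 5.6 already names R, survival status is already collected (section 4.7), and no further participants or visits are needed. The one visible downside is that reported incidences will be slightly lower than Kaplan–Meier would show.
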